### Technical Aspects of mHealth Component

The app and database are hosted at a Health Insurance Portability and Accountability (HIPPA)-compliant Canadian Provincial Crown Corporation providing sufficient reliability to maintain 99.999% uptime to meet the study needs. The field interface includes automated BP measurements by CHWs trained to do BP measurements according to the guidelines. The Bluetooth-enabled automated BP device (A&D Medical, UA-767PBT-C, San Jose, California) then transmits information via Bluetooth to the Android or BlackBerry mobile device carried by the CHW. The requirements of the app are listed in Textbox 2. The tools were tested and validated in pilot focus groups in participating communities.

The messages will be sent via a central app and database server that is ISO1348 and Food and Drug Administration–certified and brokered by an International SMS Gateway to study participants. To facilitate the BP measurement and interaction between patient and provider, algorithms were developed both at the app server level (in the cloud) and on Android/Blackberry-based devices for deployment in the field.

### Blood Pressure Control Study and Primary and Secondary Outcomes

For the BP control study, the primary outcome is the difference between the two groups in BP change from baseline to study end (both systolic and diastolic). One year was chosen as a target for BP monitoring to allow for sufficient measurements and to reduce the Hawthorne effect, in which improved BP control from better adherence might occur for the period after study enrolment [34]. To reduce the effect of regression to the mean, the baseline BP was defined as the mean of the BP readings (each mean of three measures) taken with the A&D UA-767PBT-C in the first 2 months after enrolling in the study. The final BP measurement is the mean of the last 2 to 3 measurement days, usually in the last 2 months, to reduce variability from a single set of readings. The secondary outcome is the proportion of participants achieving BP control during the study period.

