**Methods:**

This prospective, randomized blinded allocation study enrolls both adults with uncontrolled hypertension (medicated or unmedicated) and those without hypertension but at high risk of developing this condition who participate in a BP screening study. Participants will be followed for at least 12 months.

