*Project 2* is a substudy to determine whether the sodium consumption of Indigenous people can be modified to help prevent hypertension. The goal was to plan and implement a food procurement policy for reducing sodium and fat intake from commercial food sources in an isolated Northern Indigenous community. This was approached by collating scientific evidence and existing policy recommendations, engaging community leaders and local food suppliers, and developing a policy approach for commercial food procurement practices. Evaluation includes process measures and examination of successes and barriers to implementation.

*Project 3* entails the development of a closed loop app to transmit BP results taken by the CHR in Canada and the CHW in Tanzania to the health care provider and to the participant in a manner consistent with personal health privacy rules in each country.

*Project 4* includes the development of a guidelines-based set of SMS messages in English that are culturally appropriate for Canadian First Nations communities and a set of SMS messages in Swahili that are culturally specific and appropriate for rural Tanzanian communities.

*Project 5* will evaluate the impact of the active and passive messages together, compared with that of passive messages alone on BP control over 1 year through a prospective, pragmatic, randomized controlled trial in both Canada and Tanzania.

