Eligible participants were registered online. At registration, they were randomized electronically to receive active and passive SMS messages or passive only, and their names were then listed on the Dream-Global mobile app on the smartphone used by the Home and Community Care nurse or CHR in their community. BP was measured with the A&D UA-767PBT-C monitor (A&D Medical, San Jose, CA) to test that it was being transmitted properly; an SMS message to the participant’s registered mobile phone, with the BP reading, was the confirmation of transmission. The Home and Community Care nurse and CHR were trained to take three BP readings with this device. The study server was programmed in such a manner that it waits for up to three readings and then sends their mean to the participant’s own phone. Randomization through the study server ensured that participants and study personnel were blind to the allocation.

The baseline BP was defined as the mean of all readings from the A&D device in the first 2 months after randomization. If the average BP was uncontrolled during the first 2 months, the patient was identified as being in the BP lowering study; otherwise, they were followed up for BP screening. BP readings were stored on the central server, and deidentified data were transferred monthly to the data analysis center in Ottawa.

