### Canada-Specific Considerations

The Canadian arm of the project was carried out in six Indigenous communities located in three different geographic regions, including Ontario’s Manitoulin Island, the James Bay Coast of Quebec, and the north shore of New Brunswick. Recruitment into the study began in the spring of 2013 and was completed by November 2015. The last patient exited the study at the end of 2016. Study participants were followed for a period of at least 1 year. Communities were selected through a semirandom method. Canadian Indigenous communities can be found on an interactive map maintained by the Government of Canada with profiles, including population information [28]. Potential communities included those with a population of at least 3000, existing 3G mobile phone service, stable governance, and a clinical champion to serve as a bridge between the Dream-Global study researchers and the community. Potential communities were listed and put into a random order. They were contacted one by one until it was felt that sufficient communities had been contacted to make the planned study enrollment. Communities were later assessed with the Intervention and Research Readiness Engagement and Assessment of Community Health Care (iRREACH) tool (see below) to determine their readiness for research and the necessary study adaptations required to meet their needs [24].

Following an invitation by the community to discuss the study, a visit was arranged with the Canadian study lead (ST) and study staff (NP) to introduce the Dream-Global research program. This was followed by another visit to determine research readiness with the iRREACH community research participation tool [24]. A Band or Tribal Council resolution was required to ensure that the study was endorsed by the community leadership. This was particularly important because the nonmedical worker, or CHR, was central to the functioning of the study. The CHR was not compensated by the study but rather by the community who felt that the study was of sufficient importance, including research capacity development to provide enough of the CHR’s time to manage hypertension (typically 1 day per week).

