### Statistical Analysis

All patients who receive at least one SMS message and for whom data for one or more follow-up BP reading is available will be included in the efficacy and safety analyses.

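### The final blood pressure has no anchor at 12 months and is not kept apart from the baseline window, so some participants get a mistimed or diluted primary outcome

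*Protocol article*

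**What the plan says.** - **Final value.** The outcomes section (Blood Pressure Control Study and Primary and Secondary Outcomes) measures change from baseline to study end, systolic and diastolic, and defines the end value: "The final BP measurement is the mean of the last 2 to 3 measurement days, usually in the last 2 months". The same section calls one year a target for monitoring, chosen to give enough measurements and to reduce the Hawthorne effect after enrolment.
- **Question.** Under Study Goals, Project 5 evaluates active plus passive messages "compared with that of passive messages alone on BP control over 1 year".
- **Follow-up.** The abstract says: "Participants will be followed for at least 12 months". Canada-Specific Considerations repeats the one-year minimum. Neither gives a maximum. Canadian recruitment ran from spring 2013 to November 2015, and the last participant left at the end of 2016.
- **Baseline.** Blood Pressure Screening: Canada says: "The baseline BP was defined as the mean of all readings from the A&D device in the first 2 months after randomization".
- **Analysis set.** Statistical Analysis includes participants who received at least one message and "for whom data for one or more follow-up BP reading is available". It sets no minimum length of follow-up.

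**The concern.** The end value is defined by its position in a person's sequence of visits, not by time since randomization. Three things follow.

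1. **Time point.** The trial question is posed over one year, but the end value falls wherever a person's measurements end. A result at study end and a result at one year agree only if nearly everyone stops near month 12, which the article does not require.
2. **Early leavers.** Someone who stops attending at month 3 or 4 is in the analysis set and is scored then. This carries an early value into an outcome whose one-year target was meant to get past early enrolment effects.
3. **Overlap with baseline.** No rule stops a measurement day in the first 2 months from counting in both baseline and final BP. Where it counts in both, part of the measured change is baseline minus baseline.

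At stake is the meaning of the primary result and, to an unknown degree, its size. Overlap and early scoring would usually pull the difference between arms toward zero.

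**Working it through.** **1. The plan's own figure.** Inputs from Sample Size: diastolic difference 11.6 − 6.8 = 4.8 mm Hg; SDs 10.6 and 11; intraclass correlation 0.0133; inflation factor 1.1729; 176 per group; power 97%.

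- Pooled SD = √[(10.6² + 11²)/2] = 10.80.
- The inflation factor equals 1 + 13 × 0.0133 = 1.1729.
- Effective n per group = 176/1.1729 = 150.06.
- Power for 4.8 mm Hg, two-sided α = 0.05 (assumed, as α is not stated) = 97.06%.

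The stated 97% reproduces. It does not depend on when the final reading is taken, so the sample size calculation is not at issue here.

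**2. Times the rules permit.** From November 2015 to the end of 2016 is 13 to 14 months, the longest possible follow-up for the last recruits. A spring 2013 recruit kept until the end of 2016 would have 42 to 45 months. That is an outer limit, because the article gives no individual exit dates. At the short end, one follow-up reading is enough to be analysed, so no lower limit close to 12 months applies.

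**3. Share of the final mean drawn from baseline days.** Let k be the number of measurement days after month 2 and L the number of days averaged (2 or 3). If enough earlier days exist to fill L, the share is (L − k)/L when k < L, and 0 otherwise.

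| k | L = 2 | L = 3 |
|---|---|---|
| 1 | 1/2 | 2/3 |
| 2 | 0 | 1/3 |
| 3 or more | 0 | 0 |

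If the reused baseline days average about the same as that person's whole baseline, the measured change is about (1 − share) of the true change. For k = 1 that is about 1/2 (L = 2) or 1/3 (L = 3).

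**4. Illustrative effect on the group difference.** The article does not give the proportion of participants with k = 1. Assume a proportion f, equal in both arms, with the same true effect as everyone else and the SD unchanged. The expected difference is then 4.8 × (1 − f × share). Power is at the planned 176 per group with the inflation factor as above.

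| f (assumed) | L = 2: difference, power | L = 3: difference, power |
|---|---|---|
| 10% | 4.56 mm Hg, 95.5% | 4.48 mm Hg, 94.9% |
| 20% | 4.32 mm Hg, 93.4% | 4.16 mm Hg, 91.6% |
| 30% | 4.08 mm Hg, 90.5% | 3.84 mm Hg, 86.8% |

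For example, f = 20% and L = 3 gives 4.8 × (1 − 0.20 × 2/3) = 4.16. The table shows how the dilution works; it does not estimate what happened in this trial.

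**The case against.** The best defence is that the article, read as a whole, points to an end value near or beyond month 10: follow-up is at least a year, one year is the monitoring target, and the final days usually lie in the last 2 months. The last exit, 13 to 14 months after recruitment closed in November 2015, fits roughly one year per person. This stands as a description of the typical participant. It does not say how the exceptions, which the word *usually* concedes, are scored.

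A reader might go further in four ways, and the documents do not support any of them.

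- **Final values actually ranging from weeks to about three and a half years.** The rules permit this. The article does not say that early recruits stayed until 2016 or that many people left early.
- **Change of zero because baseline and final days coincide fully.** This needs a follow-up reading to include one taken within the first 2 months. The more natural meaning is a reading after that window, and then a person seen only in the first 2 months is not analysed. Partial overlap survives on that meaning.
- **Arms differing in attendance because only the active arm is told to act on a high reading.** The app requirements advise those participants to see their health care provider. Study readings are taken by the community health worker or nurse, so this is not an instruction to attend for measurement. Participants and staff are described as blinded, and allocation is blocked within community, so enrolment dates should be close to balanced.
- **No information about one year at all.** If most final values fall near month 12, the estimate would be close to a one-year effect.

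It can also be said that the choice of 2 or 3 days and the handling of early leavers belong in an analysis plan that is not shown. That is fair for the number of days. The rule that locates the final value is, however, stated in the article, and it is that rule which lacks a time anchor and allows the overlap.

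**Conclusion.** The point holds in a limited form. As written, the final-value rule has no anchor at 12 months, scores early leavers when they stop, and lets baseline days into the final mean. For a participant with one measurement day after month 2, 1/2 or 2/3 of the final mean is baseline, and the measured change falls to about 1/2 or 1/3. This follows from the stated rules, given that the person has enough baseline days to fill the average and that those days are typical of that person's baseline.

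The number of people affected and the length of follow-up past 12 months cannot be obtained from the article. If 10% to 30% were affected in each arm (assumed), the planning difference of 4.8 mm Hg would become 4.56 to 3.84 mm Hg. The main harm is dilution and an unclear time point. Bias between arms would need differential attendance, which the documents do not show.

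**What to change.** 1. Exclude every measurement day in the first 2 months after randomization from the final BP.
2. Define the primary final BP as the mean of all study-device measurement days in a pre-specified window around month 12, for example months 10 to 14. This also removes the choice between 2 and 3 days.
3. Let other post-baseline readings enter through a repeated-measures model, so that participants without a reading in the window still contribute.
4. Reconcile study end in the outcomes section with one year in Project 5, so that both name the same time point.
5. Report the present rule, the last 2 to 3 days, as a sensitivity analysis, with the number of participants whose final mean includes baseline days and the distribution of time from randomization to final value.

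The cost is small, because the readings are already stored on the central server and no new data are needed. There are two downsides. Participants with no reading in the window contribute only through the model and its assumptions. And since the last participant finished in December 2016, the new definition must be fixed before any unblinded analysis and reported as a change.

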## Results

The iRREACH tool was developed and used in all study sites in both countries [24]. Text messages derived from the Hypertension Canada Clinical Practice Guidelines were developed and revised based on focus groups in both countries as has been described [26]. A process evaluation is being developed [35]. Six communities were enrolled in the study in Canada, and recruitment was completed in November 2015. The last patient completed the study in December 2016. In total, 234 participants enrolled in the program and had at least one set of transmitted BP readings.

## Discussion

The purpose of this research program is to integrate technologic solutions with innovations in health service delivery to improve the treatment and control of hypertension. This requires integration of the scientific and social aspects of this study with business and governmental partners to design proper public-private partnerships that can be sustainable over time. Users and health care providers are involved in the development and refinement of this technology from its outset to ensure that it is useful for them. The data gathered will hopefully be of great interest to businesses and policy makers for developing ongoing sustainable business models and for scaling up in more communities. It will also inform community decision makers and governmental partners so they can promote policy changes. One marker of success for this project will be obtaining funding from Health Canada to maintain the program for the communities participating in Dream-Global, as well as others who become interested in participating at study end.

In conclusion, this study is expected to provide useful insights into the acceptability and effectiveness of an innovative system of community-based screening, treatment, and follow-up for hypertension in remote Indigenous communities in Canada. If it proves successful in this environment, then it should also be beneficial in nonindigenous settings in rural and remote areas, as well as urban settings. This work will expand an already successful body of research on bringing clinical evidence into daily practice for hypertension and can serve as a model for addressing other noncommunicable diseases in settings with limited access to health care resources. Integrating innovations in technology, health service delivery, and business models is a novel potential approach to achieve sustainable control and prevention of hypertension in particular and to address the *implementation gap* in chronic diseases in general. We will demonstrate whether the simple yet practical solution of linking hypertensive individuals with their health care providers and their personal health and medical records through SMS technology on mobile phones will lead to improved BP control and, by extension, improved outcomes.

## Appendix

Multimedia Appendix 1 CIHR peer-review report.

## Abbreviations

AE: adverse events
BCW: Behavioral Change Wheel
BP: blood pressure
CBPR: community-based participatory research
CHR: community health resource
CHW: community health workers
DMO: district medical officer
DREAM3: Diabetes Risk Evaluation and Management
GACD: Global Alliance on Chronic Disease
iRREACH: Intervention and Research Readiness Engagement and Assessment of Community Health Care
LMIC: lower- and middle-income country
NIMR: National Institute of Medical Research
RCT: randomized controlled trial
RMO: regional medical officer
SMS: short message service
TCPS2: Tri-Council Policy Statement 2
